## Abstract

**Background:**

Intracerebral hemorrhage (ICH) accounts for 15% of strokes with high mortality and limited treatment options. Cerebrolysin, a neuropeptide preparation with multimodal neuroprotective properties, has shown promise in acute ischemic stroke but remains inadequately studied in ICH.

**Methods:**

CLINCH is an investigator led, academic driven multicenter, prospective, randomized, open-label, blinded endpoint (PROBE) phase IV pilot study evaluating cerebrolysin in primary lobar ICH. We will randomize 88 patients with lobar ICH (30–80 mL; GCS 8–15; National Institutes of Health Stroke Scale, NIHSS ≥8) within 6 h of onset in a 1:1 ratio to receive either intravenous cerebrolysin (50 mL daily for 14 days) plus standard care including intensive rehabilitation, or standard care alone. Randomization will be stratified by ICH volume (30–50 vs. 51–80 mL) and GCS (8–12 vs. 13–15). Primary endpoints include 90-day mortality (safety) and functional independence (modified Rankin Scale score, mRS 0–2) at 90 days (efficacy). Secondary endpoints include neurological improvement on NIHSS, ordinal mRS shift, Barthel Index, hematoma expansion, and serious adverse events. Blinded assessors will evaluate clinical outcomes, with central adjudication of neuroimaging.

**Discussion:**

This trial addresses critical limitations of previous ICH neuroprotection studies by focusing on lobar hemorrhages, implementing an ultra-early treatment window (≤6 h), and combining neuroprotection with intensive rehabilitation. The restrictive eligibility criteria may limit generalizability but enhance the likelihood of detecting treatment effects. If positive, results would support a larger confirmatory trial and inform the sample size.

## Introduction

Intracerebral hemorrhage (ICH) accounts for approximately 15% of all strokes and carries substantial morbidity and mortality. Treatment decisions depend on multiple factors, including the patient’s age, comorbidities, clinical presentation, and neuroimaging (1). Over the last three decades, clinical trials in acute care and prevention have revolutionized everyday clinical practice in a stroke unit. However, the research on neuroprotection and neuroplasticity remains inconclusive (2, 3).

Several agents tested for neuroprotective effects after ischemic stroke, including verapamil, statins, argatroban, and glibenclamide (4) yield mostly neutral results. However, no medicinal product has been proven effective in ICH, neither to prevent direct brain damage nor to improve the long-term functional outcome. Hemostatic treatments such as tranexamic acid or factor VIIa have failed to show efficacy. At the same time, the clinical benefit from non-vitamin K oral anticoagulants (NOAC) reversal therapy is still uncertain and limited to the OAC-related hemorrhages (5, 6). Currently, the only evidence-based pharmacological intervention that improves outcomes after ICH is a treatment bundle of intensive blood pressure lowering combined with body temperature and glycemia control (7–10). However, hypoglycemic events linked to tight glucose control may be associated with increased mortality (11). The ENRICH trial has shown the benefit of minimally invasive surgical evacuation of moderately large lobar hematomas (12), which the recently announced MIND trial has partly supported (13).

Cerebrolysin is a mixture of peptides and amino acids isolated from purified porcine brain tissue with demonstrated anti-inflammatory activity (14). Its multipeptide composition confers multimodal effects on Tumor Necrosis Factor alpha (TNF-α), the Vascular Endothelial Growth Factor (VEGF), the Insulin-like Growth Factor (IGF-1) or the brain-derived NTF (BDNF) (15). In animal models, cerebrolysin positively affected behavioral performance, GABAergic synaptic current, as well as adrenergic and muscarinic modulation (16). Preclinical studies demonstrate its ability to inhibit neuroinflammation and apoptosis (17–20).

The proposed mechanisms by which cerebrolysin may improve the outcome after ICH include: (i) reduction of perihematomal inflammation through inhibition of pro-inflammatory cytokines; (ii) attenuation of excitotoxicity and oxidative stress in neurons surrounding the hematoma; (iii) promotion of blood–brain barrier integrity, potentially reducing edema formation; (iv) enhancement of neuroplasticity the recovery phase.

Clinical development of cerebrolysin demonstrates that this medication is generally safe and well-tolerated. In moderately-to-severe cortical syndromes, it augments early intensive post-ischemic stroke rehabilitation, resulting in statistically and clinically significant functional improvement (21–27). According to the European Academy of Neurology and the European Federation of Neurorehabilitation Societies guidelines, there are two interventions recommended to support early motor rehabilitation after acute ischemic stroke: (i) intravenous cerebrolysin 30 mL/day for a minimum of 10 days and (ii) citalopram 20 mg/day (28).

Conflicting conclusions of metaanalyses are caused by differences in the treatment window that in the neutral analysis excluded positive CARS-1/CARS-2 trials and were performed before the recently published ESCAS trial (DOI 10.1007/s10072-017-3214-0) (29). However, more recent studies also prove its’ positive effect on the risk of hemorrhagic transformation and functional outcome in acute ischemic stroke treated with reperfusion therapies (30–34).

Besides, the European Stroke Organization and the European Academy of Neurology in their guideline published in 2021 highlighted that there are not enough randomized clinical trials to confirm effectiveness of any mono- or polytherapy in the prevention of post-stroke cognitive functions decline. It was noted that the lack of clear definition of cognitive function results in a lack of agreement on what tests should be performed to measure these functions. While acknowledging cerebrolysin’s potential positive effects in vascular dementia, these guidelines highlighted insufficient data confirming effectiveness in post-stroke cognitive impairment (35).

To date no approved medicine mitigates the neurological and functional effects of hemorrhagic stroke. There is limited innovation in the development of novel neuroprotective therapeutics for ICH. Results from ischemic stroke trials provide a good rationale for investigating cerebrolysin in a well-designed randomized trial for the hyperacute ICH. One single study on an animal model of hemorrhagic stroke showed that administration of cerebrolysin results in reduced mortality and improved neurological outcome (36).

The observational retrospective study from 2019 that evaluated cerebrolysin treatment in patients with a minimally conscious state (MCS) observed a statistically significant improvement in the level of consciousness regardless the type of stroke (ischemic, hemorrhagic) (37).

Two trials have previously assessed cerebrolysin’s efficacy and safety in ICH. The first one demonstrating no effect after a 10-day treatment course. From the current perspective, those results must be reassessed due to several methodological limitations and advances in stroke care standards. The trial was conducted at a single center and enrolled patients with basal ganglia hematomas in whom neuroprotective and neuroregenerative effects are inherently challenging to demonstrate. The outcome measures were non-standard compared to those used generally for reporting stroke outcomes. Long-term outcomes were not reported, and the intervention did not involve early intensive rehabilitation (important for benefit from the synergistic effect of cerebrolysin and rehabilitation) and was initiated in a 6- to 24-h time window (38). This could also have affected the neutral outcome, as hematoma growth occurs mainly within 6 h of symptom onset (39). Another recent study showed a positive effect of cerebrolysion on functional outcome measured on the modified Rankin Scale (mRS) and Barthel Index and also reduced 6-month mortality (40) dose used in these patients was 30 mL daily over 21 days. Time from onset to needle was predefined as 12 h, nevertheless the patients were treated beyond 13 h of onset and less than 40% experienced lobar ICH.

The present CLINCH trial addresses these limitations by: (i) focusing exclusively on lobar hemorrhages where neuroprotective effects may be more readily detectable; (ii) implementing a pragmatic but narrow 6-h treatment window to consume the potentially effect on hematoma expansion; (iii) utilizing standardized, internationally recognized outcome measures; (iv) employing a multimodal assessment approach combining clinical, functional, and imaging outcomes; and most importantly (v) incorporating early intensive rehabilitation to maximize potential recovery benefits.

In Poland, cerebrolysin is currently registered for the treatment of organic disorders, including mild dementia in 5–50 mL daily intravenous infusions for 10–20 days. The clinical experience with cerebrolysin in acute stroke (both ischemic and hemorrhagic) includes 20–50 mL infusions administered once daily in cycles between 10 and 21 days.

Based on nonclinical and clinical study results, participants may experience clinical benefits from study participation, though direct benefits cannot be guaranteed. The investigator at each study site (or delegate) will protect the wellbeing of subjects.

## Methods and analysis

### Study design and settings

This is an investigator-initiated, academic driven hospital-based, multicenter, prospective, randomized, open-label, blinded endpoint (PROBE), phase IV parallel-group trial planned in Polish stroke units with access to rehabilitation wards. It is aimed at the population of patients who are currently lacking effective alternative therapies (NCT06899464).

The Faculty of Medicine, Collegium Medicum, Cardinal Stefan Wyszynski University in Warsaw, Poland, serves as the study sponsor.

A complete list of participating sites is provided on the clinicaltrials.gov website.

The study objective is to evaluate if a 14-day cerebrolysin treatment initiated within 6 h of onset of a primary lobar hemorrhage in addition to standard of care that includes early intensive rehabilitation is safe and feasible, affects hematoma growth and improves functional outcome.

Enrollment in the study is expected to reach 88 subjects over a 24-month period, and study completion (including follow-up) is anticipated within 15 months. The end of the study is defined as the date of the last patient’s last visit (LPLV). The sample size has been calculated based on the recent only positive trial in which patients with any type of ICH (including those with predominant basal ganglia involvement) and smaller volume (up to 25 mL) had 59.4% 6-month survival vs. 27.8% survival in patients receiving best medical treatment. Under the assumption of (i) similar absolute difference of 30%, (ii) alpha 0.05, and (iii) beta 0.80, we calculated the sample size for *N* = 88 (42 patients in each arm plus 5% for potential lost to follow-up) (40).

The PROBE design was chosen to simulate real-world practice, minimize cost and facilitate patient recruitment. Trial allocation will be known to investigators and patients, while study endpoints will be assessed by the blinded independent adjudicators.

The study protocol follows the Recommendations of Interventional Trials (SPIRIT) guidelines^1^.

### Participants

The study participants will be patients with acute ICH in whom allocated treatment can be initiated within 6 h of stroke onset and in whom a clinically meaningful benefit from treatment is considered possible. The full eligibility criteria are listed in Table 1.

**Table 1 tab1:** Inclusion and exclusion criteria.

Inclusion criteria	Exclusion criteria
1. Age 18–80 years	1. Hemorrhage caused by head trauma
2. NIHSS ≥8 at randomization	2. Medical history or neuroimaging findings suggestive of ruptured aneurysm, arteriovenous malformation (AVM), vascular anomaly, Moyamoya disease, venous sinus thrombosis, mass or tumor, hemorrhagic transformation of an ischemic infarct
3. Time from stroke onset <6h*	3. Intraventricular extension of the hemorrhage visually involving >50% of either of the lateral ventricles
4. Pre-randomization head CT demonstrating an acute, primary lobar ICH	4. Thalamic and basal ganglia ICH
5. ICH volume 30–80 mL	5. Infratentorial parenchymal hemorrhage, including midbrain, pons or cerebellum
6. Glasgow Coma Score (GCS) 8–15	6. Current use of low molecular weight heparins in therapeutic dose
7. No history of prior stroke	7. Uncorrected coagulopathy or known clotting disorder
8. Pre-stroke independence (modified Rankin Score 0–2)	8. Platelet count < 75,000, International Normalized Ratio (INR) > 1.4 after correction
9. Ability to provide informed consent	9. End stage renal disease
	10. Patients with a mechanical heart valve
	11. End-stage liver disease
	12. Epilepsy with grand mal seizure
	13. History of drug or alcohol use or dependence that, in the opinion of the site investigator, would interfere with adherence to study requirements
	14. Positive urine or serum pregnancy test in female subjects without documented history of surgical sterilization or post-menopausal
	15. Known life-expectancy of less than 6 months
	16. No reasonable expectation of recovery, Do-Not-Resuscitate (DNR), or comfort measures only prior to randomization
	17. Participation in a concurrent interventional medical investigation or clinical trial
	18. Inability or unwillingness of subject or legal guardian/representative to give written informed consent
	19. Any condition that would represent a contraindication for cerebrolysin administration

*Cerebrolysin treatment can be initiated within 6 h after the onset of stroke. If the actual time of onset is unclear, the time the subject was last known to be well will be used instead.

Written informed consent will be obtained by the investigator from each subject or their legal guardian before enrollment. The informed consent form (ICF) includes consent for pseudonymized data use according to the European Union General Data Protection Regulation (GDPR) requirements.

All enrolled subjects will be assigned a unique identification number in ascending order. Subject numbers will be used in the case report form (CRF). A list identifying the subjects by subject number will be kept in the site files.

### Intervention

The selected cerebrolysin dosage of 50 mL daily for 14 consecutive days is based on several considerations: (i) efficacy data from previous ischemic stroke trials suggesting that higher doses (30–50 mL) may produce more robust effects than lower doses; (ii) safety profile established in previous clinical studies confirming tolerability of this dosing regimen; (iii) the need for a sufficient treatment duration to potentially impact both acute (hematoma expansion, perihematomal edema) and subacute (inflammation, apoptosis) pathophysiological processes after ICH, and to support intensive rehabilitation.

The 6-h treatment window was selected based on the temporal profile of hematoma expansion in primary ICH, balancing (i) practical feasibility of patient identification, consent, and randomization; (ii) opportunity to affect hematoma expansion, which is the key determinant of functional outcome; (iii) 4- to 6-h therapeutic window for traumatic brain injury; and (iv) 8-h time window in the cerebrolysin thrombectomy trials.

The marketed product cerebrolysin 215.2 mg/mL solution for injection and infusion will be used as the study drug. For details and preparation instructions, please refer to the cerebrolysin Summary of Product Characteristics and package leaflet approved by the President of the Office for Registration of Medicinal Products, Medical Devices and Biocidal Products in Poland.

The cerebrolysin solution should not be mixed with amino acid solutions in one infusion. Vitamins and cardiovascular drugs may be administered simultaneously; however, they should not be mixed with a cerebrolysin solution in one infusion bag.

All subjects will receive care in the stroke unit and will receive stroke treatment and diagnosis according to Polish and international guidelines.

There are six time points of assessment (Table 2).

**Table 2 tab2:** Time points of assessment.

Time range	Assessment point
t0	Stroke onset
Day 1	≤5,5 h after t0: Baseline assessment prior to enrollment and randomization
Day 1	≤ 6 h after t0: Randomization followed by first dose of cerebrolysin (dosing in treatment arm only)
Day 2	24 ± 4 h from randomization
Day 7	7 days ±12 h from randomization
Day 14	14 days ±1 day from randomization
Day 30	30 days ± 2 days from Day 1
Day 90	90 days ± 7 days from Day 1

At baseline, brain non-contrast computed tomography (NCCT) and computed tomography angiography (CTA) scans, demographics, medical history, physical examination, vital signs, clinical scores [NIHSS, premorbid mRS and Barthel index (BI)], and eligibility criteria review will be recorded. The ICF signature will be collected prior to any study-specific procedure. Procedures completed as part of the standard of care but prior to ICF signature may be used for eligibility verification and baseline assessments.

All subjects, regardless of arm assignment, will have laboratory tests collected, and stroke treatment and rehabilitation programs will be implemented at the investigators’ discretion. Throughout the study, concomitant medications and adverse events (AEs) will be collected. Results will be investigator-assessed using Common Terminology Criteria for Adverse Events (CTCAE) version 5.0 (published November 27th, 2017).

Eight-eight subjects will be enrolled at 1:1 ratio.

After randomization, 44 subjects will receive an intravenous infusion of 50 mL cerebrolysin mixed with 250 mL of saline over 30 min once daily from Day 1 to Day 14 (14 consecutive days of treatment) plus standard of care treatment at the discretion of the investigator (treatment arm). The first dose of cerebrolysin must be administered as soon as possible and within 6 h from ICH onset. Another 44 subjects will be subject to receive standard of care treatment alone at the discretion of the investigator (control arm).

All subjects will be scheduled for intensive motor and/or speech and language rehabilitation, as stated in Polish reimbursement guidelines (120 min Per patient in patients with BI≥75 and 180 min Per patient in those with BI<75 day 5 days a week; additionally, all patients undergo 60 min Rehabilitation on Saturdays; in aphasic patients, speech therapy is additionally applied 5 days a week for 30 min).

Cerebrolysin will be administered once daily from Day 1 to Day 14 or until the end of treatment due to death, intolerable adverse events, subject loss to follow-up, consent withdrawal or study termination. Patients who discontinue treatment and receive at least one dose of cerebrolysin will be asked to attend all follow-up visits. A subject is considered as lost to follow-up when all follow-up efforts have been unsuccessful.

All subjects will undergo neurological assessments conducted by experienced stroke neurologists designated by the investigator: National Institutes of Health Stroke Scale (NIHSS) on Day 1 (at baseline), Day 2, Day 7, Day 14, Day 30, and Day 90; modified Rankin Scale (mRS) and BI on Day 1 (premorbid), Day 30 and Day 90.

The baseline brain NCCT and CTA will be completed on Day 1 (baseline) and the follow-up CT scan on Day 2 (24 ± 4 h from randomization) and day 14 ± 1 right after treatment termination. This will allow to assess the evolution of swelling which also reflects the status of blood–brain barrier permeability. The magnetic resonance imaging (MRI) scan will be completed on Day 90 ± 7 (41).

If on-site neurological assessment is not possible, investigators should schedule a telephone visit and collect information remotely.

Please refer to Table 3 for study schedule details. The trial assessment flowchart is presented in Figure 1.

**Table 3 tab3:** Treatment schedule.

Treatment/procedure	Day 1 (screening)	Day 1 (baseline)	Day 2	Day 7	Day 14	Day 30	Day 90
Informed consent	x						
Eligibility assessment	x						
Demographics	x						
Medical history	x						
Physical examination*	x					x	x
ECOG score	x					x	x
Vital signs**	x					x	x
Pregnancy test, if applicable	x						
CT scan***	x		x		x		
MRI scan							x
mRS		x				x	x
NIHSS		x	x	x	x	x	x
Barthel index		x				x	x
Adverse events	x	x	x	x	x	x	
Concomitant medications	x	x	x	x	x	x	x
Randomization		x					
Cerebrolysin treatment (if allocated)		x	x	x	x		

*Physical examination: assessment of general appearance and review of organ systems (dermatologic, head, eyes, ears, nose, mouth/throat/neck, thyroid, lymph nodes, respiratory, cardiovascular, gastrointestinal, extremities, musculoskeletal, and neurologic systems). **Vital signs: pulse rate, respiratory rate, O2 saturation, body temperature, and blood pressure (systolic/diastolic, subjects should be supine/sitting for 5 min before assessment). ***Baseline brain NCCT and CTA scan on Day 1 (baseline) and follow-up CT scan on Day 2 (24 ± 4 h from randomization), and Day 14 (±1 day from randomization).

**Figure 1 fig1:**

Trial assessments flowchart.

### Adverse events

At the time of study completion or early withdrawal, subjects will be asked directly about any AEs, concomitant medications, and concurrent procedures, which bias will be recorded in the source documentation and CRF. At the final study visit, subjects with ongoing AEs that are considered by the investigator to be study drug-related will be requested to continue to follow-up with the investigator until the AE resolves, stabilizes, or follow-up is no longer possible/necessary. Subjects will continue their prescribed medications and rehabilitation program following study completion. Any serious adverse event (SAE) that occurs while on study must be reported to the sponsor/designee for the study within 24 h after the site becomes aware of the event.

An SAE is defined as any untoward medical occurrence that at any tested drug dose: results in death, is life-threatening, requires hospitalization or prolongs existing hospitalization, results in persistent disability, is a congenital anomaly/birth defect or is medically important.

Medical and scientific judgment must be exercised in determining whether an AE is considered “medically important.”

Hospitalization is defined as (i) admission to a hospital/inpatient facility or (ii) staying at the hospital for treatment or observation for more than 24 h. Events leading to hospitalizations for the following reasons should not be reported as SAEs: (i) trial-related purposes not associated with any deterioration in condition, (ii) precautionary hospitalization for dosing of the study drug without any associated deterioration, (iii) social reasons in the absence of any deterioration in the patient’s general condition, (iv) elective surgery or other scheduled hospitalizations that were planned before the patient was enrolled for this trial.

Good Clinical Practice (GCP), European Medicines Agency pharmacovigilance, and national regulations for reporting adverse drug reactions (ADRs) and suspected unexpected serious adverse events (SUSAR) apply to both arms.

### Allocation

Participants will be stratified according to baseline ICH volume (30–50 mL vs. 51–80 mL) and Glasgow Coma Scale score (8–12 vs. 13–15) using randomised permuted blocks (block size 4) in a 1:1 ratio. Randomization will occur after baseline assessment using a computer-generated random allocation sequence. The treatment assignment will be provided to the site once a subject meets all eligibility criteria. The randomizing physician will be blinded to allocated treatment prior to randomization. Blocking details will be included in the Randomization Plan managed by the sponsor and will be unavailable to investigators enrolling participants and assigning interventions.

Subjects, healthcare providers, and data collectors will be aware of treatment allocation, while the independent outcome adjudicator will remain blinded.

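### The article prints a block size of 4 although blocking details are to be withheld from enrolling investigators; with open treatment, some next allocations can be deduced

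*Protocol article*

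**What the plan says.** The Allocation section of the protocol article sets 1:1 allocation "using randomised permuted blocks (block size 4) in a 1:1 ratio" within strata formed by two bands of ICH volume and two bands of GCS, so four strata. One size is given and no other is mentioned; that it is constant throughout is an inference from this. Site is not named as a stratification factor, and the article does not say whether sites share lists or have their own.

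The same paragraph places the blocking details in a sponsor-managed Randomization Plan and says that they "will be unavailable to investigators enrolling participants and assigning interventions". It adds that a site receives an assignment only after the subject has met all eligibility criteria, and that the randomizing physician does not know it beforehand.

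Treatment is open. Study design and settings says "Trial allocation will be known to investigators and patients", and Allocation says "Subjects, healthcare providers, and data collectors will be aware of treatment allocation". Blinding applies to the 90-day clinical assessment and to the central reading of CT scans (PROBE design). The study is a "phase IV parallel-group trial planned in Polish stroke units with access to rehabilitation wards"; the article refers to the registry for the list of sites and gives no number.

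**The concern.** Block size is the central blocking detail, and it is printed together with the ratio and the strata. An enrolling investigator who reads the article therefore holds what the paragraph says is withheld. Hiding the next assignment does not prevent its deduction from past assignments that everyone on the ward can see.

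What is at stake is who gets enrolled. Most criteria in Table 1 are objective, but some depend on judgement: exclusion 16 turns in part on the expected chance of recovery, exclusion 13 on the site investigator's opinion, and the opening of Participants on whether meaningful benefit is thought possible. Those judgements concern prognosis, and the primary outcomes are 90-day mortality and functional independence. With 88 patients, a few selective decisions could matter. Blinded outcome assessment protects measurement, not selection. Adjustment for ICH volume and GCS (Statistical analysis) covers selection that acts through those two factors, but not selection on unmeasured prognosis.

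**Working it through.** The plan gives no figure for predictability, so there is none to reproduce. The sample size enters only as an input and is not disputed: "42 patients in each arm plus 5% for potential lost to follow-up" gives 84 × 1.05 = 88.2, stated as 88.

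**Inputs from the article:** block size 4, ratio 1:1, four strata, N = 88, past allocations open.

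**Assumptions:** strata equally likely; number of sites varied up to 20; lists either per site or shared.

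**Step 1. One complete block, all earlier allocations in it seen.** There are 6 equally likely orders of two A and two B.
- Certain allocations: the 4th always, and the 3rd when the first two are equal (2 of 6 orders = 1/3). Share = (1 + 1/3)/4 = 33.3%.
- Best guess (name the arm with more places left): correct with probability 1/2, 2/3, 2/3 and 1 at positions 1 to 4. Sum = 17/6; divided by 4 = 17/24 = 70.8%. A wholly unpredictable sequence gives 50%.

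**Step 2. The trial as a whole, by simulation.** For 88 patients in four strata, with incomplete last blocks:

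| What the investigator sees | Certain | Best guess correct |
|---|---|---|
| Whole stratum lists | 31.5% | 70.0% |
| Per-site lists, 5 sites | 23.8% | 66.5% |
| Per-site lists, 10 sites | 13.9% | 62.1% |
| Per-site lists, 20 sites | 5.2% | 57.2% |
| Shared lists, own patients only, 2 sites | 7.9% | 59.5% |
| Shared lists, own patients only, 5 sites | 1.3% | 54.3% |
| Shared lists, own patients only, 10 sites | 0.3% | 52.2% |
| Shared lists, own patients only, 20 sites | 0.1% | 51.2% |

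The shared-list rows favour the observer, who is assumed to know where each block starts. In patients, the range runs from 0.315 × 88 ≈ 28 with whole lists seen, through 0.238 × 88 ≈ 21 and 0.052 × 88 ≈ 5 for per-site lists at 5 and 20 sites, to 0.013 × 88 ≈ 1 for lists shared by 5 sites.

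**Step 3. Varying block sizes.** The observer is assumed to know which sizes are in use, but not their order.

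| Lists and block sizes | Certain | Best guess correct |
|---|---|---|
| Whole lists seen, 4 only | 31.5% | 70.0% |
| Whole lists seen, 4 and 6 | 5.8% | 68.4% |
| Whole lists seen, 4, 6 and 8 | 2.4% | 67.0% |
| Per-site lists, 5 sites, 4 and 6 | 4.2% | 64.4% |
| Per-site lists, 20 sites, 4 and 6 | 0.2% | 55.7% |

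Varying the sizes removes most of the certainty and little of the general guessability.

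**The case against.** The strongest reply is that the practical risk is small. Assignments are released only after eligibility is confirmed, and the randomizing physician is blind to them until then. The trial is multicenter, only ICH volume and GCS are named as stratification factors, and nothing in the article gives a recruiter sight of other sites' allocations. If lists are shared, an investigator at one of five or more sites can be certain of about 1% of allocations or fewer. The 6-hour window also limits holding a patient back for a preferred slot, and the study is called a pilot.

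The remedy has limits too. Suppose a site simply counts its own patients in a 22-patient stratum on a shared list. If it sees half of them, its guesses are right 55.9% of the time with size 4, 55.7% with 4 and 6, and 55.8% with 4, 6 and 8. In that setting the change does almost nothing. Finally, only an article is shown, so what the full protocol prints is unknown.

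Most of this stands as a limit on size. It does not remove the contradiction. The article is public, so investigators can read the block size whatever the full protocol shows, and releasing assignments late does not stop deduction from past open ones. Whether lists are shared is not stated, and with per-site lists the share is not negligible.

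A reader might infer that allocation concealment fails altogether, or that one third of allocations are predictable at every site. The article supports neither: the assignment itself stays hidden until eligibility is confirmed, and one third requires sight of a whole stratum list. Nor do varying sizes bring guessing back to 50% or remove every certain allocation.

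**Conclusion.** The point holds in a limited form. The Allocation section discloses the blocking detail that it says is withheld, and open treatment makes that detail usable. What is weakened is the unpredictability of the sequence, not the concealment of each assignment before eligibility is confirmed. The certain share ranges from about one third at most to about 1% or less, depending on list structure and number of sites, neither of which the article gives. The figures also assume equally likely strata and one constant block size. The possible harm is some selective enrolment through the few judgement-based criteria; nothing in the article shows that it will occur. This is a modest defect that is cheap to correct.

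**What to change.** Generate the list with randomly varying block sizes, for example 4 and 6, or 4, 6 and 8. If recruitment has begun, apply this to all future blocks. Record the sizes only in the restricted Randomization Plan. Reword the Allocation section so that its two statements agree, for instance by saying only that permuted blocks of undisclosed, varying size are used. Because the size is already public, deleting the number alone is not enough: the sizes in use must change. Stating whether lists are shared or kept per site would let readers judge the remaining risk.

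The cost is regenerating the list or its unused part, and a slightly larger possible imbalance between arms within a stratum. No clinical procedure changes.
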